### 7.2 Recruitment, screening and patient's instructions

The concerning patients will be screened every day by the clinicians and the study investigators during the presurgical surgical and anesthesiologic consultations. In case all inclusion and no exclusion criteria are met, the patient will be informed about the study by one of the investigators (see chapter 2.7) and orally instructed about the handling of the decolonization set. It is important that the study investigator instructs the patient (and his/her accompanying family members) directly. An instruction of the set handling by the surgeons or anesthesiologists alone will not be accepted.

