## Study Conduct

The BALGDEC trial is a single-center trial, beginning in February 2023. Only elective surgery patients with a focus on high risk patients for revision and /or SSI according to prior studies will be included, whereas patients with an extraordinary high risk for SSI or impossibility of decolonization will be excluded. At the Balgrist site, this patient population includes: immune-suppressed patients of any type, tumor surgery patients, revision surgery, patients with ASA-Scores 3-4 points or with an age of  $\geq 80$  years; independently of the presence of an orthopedic implant. The operational study team is mainly composed by two infection control nurses, an infectious diseases physician, an orthopedic surgeon with experience in decolonization studies, and the UCAR-team (Unit for Clinical and Applied Research; study nurses).

The infectious control nurses and the infectiologist provide will provide pre-operatively specific instructions regarding the decolonization measure o the patients, and randomize them (1:1) between the presence or absence of the "set" used. The decolonization set will be physically handed over during the inclusion process. The randomization occurs electronically or by prefabricated cards by another study team member not involved in the patient's information process. During decolonization, patients are asked to change the bed linen and underwear every day and not to share towels, clothes and other textiles with their family or pets. They may use their habitual parfums, but must not use other topical antiseptic agents, body lotions or moisturizer during the decolonization period.

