#### Exclusion criteria:

- Elective revision orthopedic surgery due to orthopedic infection within the last 12 months in the same area of surgery
- Emergency surgery (defined as planned surgery within the next 48 hours)
- Surgery on infected skin; or surgery under antibiotic treatment for any reason
- "Diabetic foot surgery" (distinct clinical entity; defined as below the ankle)
- Body mass index  $\geq 35$  kg/m^2 (anticipated difficulty of effective decolonization)
- Pregnancy (formality reasons)
- Intolerance or allergy to octenidin and/or ingredients in the octenisan® set
- Use of any other topical antiseptic agents other than octenisan® set (except for the duration of one day)
- Patient unable to understand; or under legal guardian for medical decisions
- Anticipated clinical follow-up of less than 6 weeks after surgery.
- ASA-Scores 1-2, and ASA-Score 5 (high risk of postoperative complications)
- Known skin colonization with antibiotic-multiresistant Gram-negative organisms defined by infection control protocols of Switzerland.

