#### 8.1.1 Intervention treatment

The duration of pre-surgical decolonization is planned to be five days. However, when this pre-surgical time period is too short, the decolonization may also start at least 3 days before surgery and may be continued up to 2 days post-surgery. In case of post-surgery application, the patient will be washed with water and octenisan® wash lotion by their treating nurses. The patient will also return the empty/used set and answer to a short questionnaire during their hospital stay. The study team will recuperate the questionnaire during hospitalization.

During decolonization, patients are asked to change the bed linen and underwear every day and not to share towels, clothes and other textiles with their family or pets. They may use their habitual perfumes, but must not use other antiseptic agents, body lotions or moisturizer during the decolonization period.

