#### 8.1.2 Control Comparator

Absence of decolonization and absence of the questionnaire.

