### 8.3 Compliance with study intervention

We assess the auto-declared compliance of the patients in the intervention (decolonization) arm via questionnaires and by recuperating the empty packages of the decolonization sets.

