### **11.2 Determination of Sample Size**

In our hospital, postoperative wound problems occur in at least 5% percent of all interventions. Incidence for both, revision surgery and/or SSI, in our selected patient population is set for 10% according to our clinical experience among the selected patient population that composes our study population.

We perform a superiority RCT with a power of 80% in favor of the decolonization. With 95% event-free surgeries in the decolonization arm versus 90% in the standard arm, we formally need 2 x 474 orthopedic surgery episodes, which we sum up to 2 x 500 surgeries (n = 1'000). A patient can be included several times as long as he/she gets not infected and has not witnessed postoperative wound problems.

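### The protocol leaves open whether future controls are taught to use the decolonization set before allocation, does not tell controls to abstain, and asks about product use only in the decolonization arm, so self-decolonization in controls could be missed

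*Protocol*

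**What the plan says.** **When instruction is given.** Section 7.2 covers patients who meet all criteria. They are informed about the trial and "orally instructed about the handling of the decolonization set", and the investigator must instruct patient and family directly. Assignment follows in 7.3. The synopsis (Study Conduct) has the infection control team give "specific instructions regarding the decolonization measure o the patients, and randomize them (1:1"). Section 9.2 puts the instruction sentence after the randomisation sentence and names no arm. The numbered list in 9.2.1 starts with information and consent and ends with randomisation and hand-out of the set as one step. It mentions no earlier training.

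**What controls may do.** Section 8.1.2 defines control as "Absence of decolonization and absence of the questionnaire". The exclusion criterion on antiseptics reads "Use of any other topical antiseptic agents other than octenisan® set (except for the duration of one day"). The behavioural restriction in 8.1.1 says patients "must not use other antiseptic agents, body lotions or moisturizer during the decolonization period", and controls have no such period.

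**What is recorded.** Section 8.3 states: "We assess the auto-declared compliance of the patients in the intervention (decolonization) arm via questionnaires", together with the return of empty packages. For both arms, the Study Schedule has rows for concomitant medication and compliance, and 9.2.2 records concomitant medications and additional interventions at Visit 2.

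**Context.** Patients are not blinded (6.2.2), and the set is on the Swiss market at about CHF 22.25 (8.1).

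**The concern.** The contrast under test is decolonization against none. If some controls decolonize themselves, the control event rate moves towards that of the active arm. A superiority comparison is then biased towards no difference.

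The protocol supplies the conditions for this. On the 7.2 wording, controls have been shown how to use the product. They know their allocation, the product can be bought, and nothing asks them to refrain. Repeat inclusion (11.2) adds a route, because a patient decolonized in one episode can be a control in a later one.

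Detection is also uneven. Non-adherence in the decolonization arm is sought by questionnaire and package count, while use in controls is not asked about. Section 11.3.2 removes significant deviators from PP, and 11.4 removes major deviations from both ITT and PP. Unequal detection can therefore affect both analysis sets. Exposure that was never recorded cannot be recovered in the analysis.

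**Working it through.** **1. The passages side by side**

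| Question | Where | What it supports |
|---|---|---|
| Instruction before allocation? | 7.2, then 7.3 | Yes, all eligible patients |
| | Synopsis, Study Conduct | Yes, by order of wording |
| | 9.2 | Mentioned after randomisation; arm not limited |
| | 9.2.1 | Randomisation and hand-out together; no prior training listed |
| Controls told to abstain? | 8.1.2 | Implied by the definition, not stated as an instruction |
| | Exclusion criteria | Other antiseptics barred; octenisan set exempt |
| | 8.1.1 | Restriction tied to the decolonization period |
| Use in controls asked about? | 8.3 | Decolonization arm only |
| | Study Schedule, 9.2.2 | Generic entries for both arms; no antiseptic wash or nasal gel item |

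**2. The plan's own sample size.** Inputs from 11.2: "We perform a superiority RCT with a power of 80% in favor of the decolonization" and "With 95% event-free surgeries in the decolonization arm versus 90% in the standard arm". That is p1 = 0.10, p2 = 0.05, d = 0.05. Section 11.3 gives two-sided alpha 0.05.

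With p̄ the mean of p1 and p2, A = √(2p̄(1−p̄)) and B = √(p1(1−p1) + p2(1−p2)):

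- A = √(2 × 0.075 × 0.925) = 0.3725; B = √(0.09 + 0.0475) = 0.3708.
- Uncorrected n = ((1.960 × 0.3725 + 0.842 × 0.3708) / 0.05)² = 434.4, so 435.
- Continuity-corrected n = (434.4/4) × (1 + √(1 + 4/(434.4 × 0.05)))² = 473.6, so **474**, the protocol's figure.

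This calculation has no allowance for contamination.

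**3. Power at 500 per arm if a share c of controls decolonizes.** Assumptions, neither given in the documents: c is unknown and is shown as a range, and those who self-decolonize get the full planned effect. Then p1 = 0.10 − 0.05c, p2 stays at 0.05 and d = p1 − 0.05.

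- Uncorrected (as for the planned Pearson chi-square): z = (d√500 − 1.960A)/B; power = Φ(z).
- Corrected (the basis that gives 474): replace 500 by m = 500 − 2/d + 1/(500d²), which inverts the correction.

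Example, c = 0.20: p1 = 0.09, d = 0.04, 1.960A = 0.7072, B = 0.3597.

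- Uncorrected: z = (0.04 × 22.361 − 0.7072)/0.3597 = 0.520, power 69.9%.
- Corrected: m = 500 − 50 + 1.25 = 451.25; z = (0.04 × 21.243 − 0.7072)/0.3597 = 0.396, power 65.4%.

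| c | Control rate | Power, corrected | Power, uncorrected |
|---|---|---|---|
| 0% | 10.00% | 82.3% | 85.2% |
| 5% | 9.75% | 78.7% | 82.1% |
| 10% | 9.50% | 74.7% | 78.4% |
| 20% | 9.00% | 65.4% | 69.9% |

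Power at 500 per arm crosses 80% at c of about 3% (corrected) or 8% (uncorrected).

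**The case against.** Several parts of the case against this point stand.

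- **Timing is not settled.** A reader of 7.2 alone might infer that every control is certainly trained before allocation. Sections 9.2 and 9.2.1 do not bear that out. The finding is an inconsistency that must be resolved.
- **Recording is not absent.** A reader might infer that product use in controls can never come to light. Concomitant medication, additional interventions and a compliance row cover both arms, and the eCRF is not shown. What the documents support is narrower: the protocol names no item asking controls about antiseptic washes or nasal gel.
- **The per-protocol rule is not one-sided.** Section 11.3.2 applies to both arms, and a control who decolonized departs from 8.1.2. Only the means of detection differ.
- **The antiseptic exclusion might be read as running through the trial.** Even on that reading it exempts the octenisan set, the product most relevant here.
- **Consent explains the procedures to everyone**, so moving the instruction will not keep controls unaware of decolonization. It does avoid giving them practical training.
- **The size is assumed.** Full effect from unsupervised use is an upper bound, and the uncorrected basis is more favourable. Both bases are therefore shown.

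None of this supplies an instruction to controls, or a specific question that would detect use.

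**Conclusion.** The concern holds in a limited form. The protocol gives conflicting accounts of when the set is taught and to whom, does not tell controls to abstain, and looks specifically for product use in one arm only. Self-decolonization in controls is therefore possible and could be missed. It would bias towards no difference and weaken the identification of deviators in the control arm.

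Under the full-effect assumption, the power lost at 500 per arm is about 3 to 4 percentage points at 5% contamination, 7 to 8 at 10%, and 15 to 17 at 20%. The documents do not show that contamination will occur at any of these levels. Nor should a reader infer that the stated sample size is wrong: 474 per arm is reproduced exactly on its own inputs.

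**What to change.** 1. In 7.2, 9.2 and the synopsis, state one order: set-handling instruction after randomisation, to the decolonization arm only. Align 9.2.1 with it.
2. Reconcile the octenisan exemption in the exclusion criteria and the antiseptic restriction in 8.1.1 with the control definition in 8.1.2, so that what applies to controls is explicit.
3. At Visit 2, which both arms attend, add an eCRF item for both arms on any antiseptic wash or nasal antiseptic use: yes/no, product, days.
4. Amend 11.4, which now drops major deviations from ITT as well as PP and so conflicts with the all-randomised ITT set in 11.3.2. Patients with such use should stay in ITT as randomised and be handled as deviators in PP by the same rule in both arms. Without this change, the new item could itself lead to exclusions from ITT.

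The cost is protocol wording, one eCRF item and a changed order of steps at enrolment. The question may slightly raise controls' awareness; asking it at Visit 2, on the day of surgery or 1 to 2 days after, limits that. No extra visit is needed and the sample size does not change.

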### 7.3 Assignment to study groups

Assignment to the study group (control versus intervention group) will be done with randomization cards (or electronically).

### 7.4 Criteria for withdrawal / discontinuation of participants

All patients are free to withdraw from participation in this study at any time, for any reason, and without

prejudice. A patient who withdraws consent by refusing to continue with study procedures/observations will be terminated from the study. The reason for withdrawal of consent will be clearly documented wherever possible. However, it is not required for patients to provide their reason.

The investigator should make every effort to address non-compliance issues and ensure that relevant study data are obtained from patients whenever possible.

To enable collection of follow-up data, the investigator may stop study treatment at any time without withdrawing the patient from the study (e.g. the patient experiences intolerable or unacceptable AEs possibly related to study treatment and where such treatment cannot be modified within the confines of the protocol).

On rare occasions, the investigator may exclude a patient from the study to protect his/her best interest e.g. to protect them from excessive risk or risk with a demonstrated lack of benefits (serious side-effects) or to maintain the integrity of the data (when participants are not following study procedures or may be deliberately providing false information). The investigator must explain to the participant the reasons. If a patient is withdrawn before completing the study, the reason for withdrawal will be entered in the electronic case report form (eCRF). Whenever possible and reasonable, the evaluations that are required at the next scheduled visit will be performed at early termination.

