#### **9.1.4 Assessments in participants who prematurely stop the study**

Participants who prematurely stop the investigation are defined as patients who withdraw consent or who, in the opinion of the investigator, are no longer eligible to participate in the study. Where possible, such patients will complete an early-termination visit to undergo all assessments applicable to the corresponding (or next) scheduled study visit. For these patients, we will record eventual adverse events, physical examination, laboratory parameters, vital signs during a follow-up period determined by clinical control, which is usually up to one-year post intervention.

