#### 11.3.2 Final analyses

The intent-to-treat (ITT) population will consist of all randomized patients. Patients will be analysed according to treatment group assignment. Patient disposition and baseline characteristics will be based on the ITT population.

The per-protocol (PP) population will consist of all randomized patients who complete the study (or who are otherwise defined as a treatment failure) according to the clinical investigation plan and who have not deviated significantly from the protocol. All efficacy analyses will be repeated using the PP population. Any analysis involving microbiological assessments will exclude patients without an assigned baseline pathogen.

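### Section 7.4 permits excluding randomized patients for not following procedures and does not separate refusing decolonization from leaving follow-up, so outcomes can be lost unequally between arms

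*Protocol*

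**What the plan says.** Two sentences in section 7.4 can end participation.

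- Consent: "A patient who withdraws consent by refusing to continue with study procedures/observations will be terminated from the study". Procedures and observations are joined by a slash, so declining the washing and declining follow-up are not told apart. Section 6.1.2 then removes from further analysis the data of anyone who withdraws consent up to one month after the last study visit.
- Discretion: "On rare occasions, the investigator may exclude a patient from the study to protect his/her best interest", or "to maintain the integrity of the data (when participants are not following study procedures or may be deliberately providing false information").

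The same section also pulls the other way: "The investigator should make every effort to address non-compliance issues and ensure that relevant study data are obtained from patients whenever possible", and "To enable collection of follow-up data, the investigator may stop study treatment at any time without withdrawing the patient from the study". Section 8.4 asks withdrawn participants to continue surveillance. Section 9.2.3 wants primary outcome data for every subject. Section 9.1.4 plans an early-termination visit where possible, and adds that "we will record eventual adverse events, physical examination, laboratory parameters, vital signs during a follow-up period determined by clinical control".

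The control is "Absence of decolonization and absence of the questionnaire" (8.1.2). Washing, nasal gel, textile rules, set return and questionnaire belong to the decolonization arm (8.1, 8.1.1), and compliance is assessed only there (8.3). For the analysis, 11.3.2 states: "The intent-to-treat (ITT) population will consist of all randomized patients".

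**The concern.** Randomization protects the comparison only if outcomes are sought for everyone randomized. An exclusion ground based on adherence acts after randomization. Here it is applied by someone who knows the allocation, and it concerns tasks that one arm has and the other hardly has. A control patient can miss a visit but cannot skip washes, fail to return a set or leave a questionnaire blank.

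If excluded patients differ in risk from those who stay, the decolonization arm is no longer comparable with the control arm. The study population is elderly or has high ASA scores, so a link between non-adherence and wound risk is plausible in either direction. The protocol gives no figure for it.

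This is distinct from section 11.4, which removes major deviators at the analysis stage. Repairing 11.4 alone would not bring back outcomes that were never recorded, or that were deleted under 6.1.2.

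**Working it through.** **1. The plan's own figure.** Inputs from 11.2 and 11.3: 10% versus 5% events, 80% power, two-sided 0.05, 1:1.

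- Uncorrected: n = [1.96·√(2·0.075·0.925) + 0.8416·√(0.10·0.90 + 0.05·0.95)]² / 0.05² = 434.4, so 435 per arm.
- With continuity correction: (n/4)·[1 + √(1 + 4/(n·0.05))]² with n = 434.4 gives 473.6, so 474 per arm.

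The stated 474 is reproduced, and the concern does not touch it. The plan then rounds up to 500 per arm.

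**2. Loss unrelated to risk.** With 500 per arm and patients removed from the decolonization arm only, power (without continuity correction) is 85.2% with no removal, 84.2% at 5% removed and 83.1% at 10% removed. There is no bias, and loss of power is not the issue.

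**3. Loss related to risk: illustration under assumptions.** The protocol states no adherence rate and no risk for non-adherers. Assume no true effect (10% in both arms), a share q of the decolonization arm removed, and removed patients at r = 2 times the risk of those who stay.

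- Risk in retained patients: p = 0.10 / (1 − q + q·r); retained n = 500·(1 − q); false benefit d = 0.10 − p.
- Chance of a significant result favouring decolonization: 1 − Φ[(1.96·s0 − d)/s1], where s0 is the pooled and s1 the unpooled standard error of the difference.

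| q | retained n | p | d (points) | s0 / s1 | one-sided false positive |
|---|---|---|---|---|---|
| 2% | 490 | 0.10/1.02 = 9.80% | 0.20 | 0.01899 / 0.01899 | 3.2% |
| 5% | 475 | 0.10/1.05 = 9.52% | 0.48 | 0.01902 / 0.01901 | 4.4% |
| 10% | 450 | 0.10/1.10 = 9.09% | 0.91 | 0.01911 / 0.01907 | 6.8% |

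The reference value is 2.5%. At r = 1 the bias is zero for any q, and if non-adherers were at lower risk the sign would reverse. The 2% and 5% rows (10 and 25 of 500 patients) fit a rule meant for rare use better than the 10% row.

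**4. The passages side by side.**

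- Section 7.4 asks for data from non-compliant patients and also lists not following procedures as a ground for exclusion.
- Section 8.4 asks withdrawn patients to continue surveillance, while 6.1.2 removes the data of those who withdraw consent.
- Section 9.2.3 wants the primary outcome for all subjects. The longer follow-up list in 9.1.4 does not name SSI or wound revision, and its early-termination visit covers only the corresponding or next scheduled visit. For an implant patient who leaves before surgery, that is not the 1-year outcome.
- Section 11.3.2 counts all randomized patients as ITT, while 7.4 allows some of them to be put out of the study.

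**The case against.** The strongest reply is that 7.4 does not turn non-adherence into removal. The exclusion is discretionary, confined to rare occasions, and listed beside deliberate falsification. The consent sentence is about a patient who withdraws consent; it does not say that skipped washes amount to withdrawal. The default in 7.4 is to address non-compliance and keep collecting data. Treatment may be stopped without leaving the study, and the adverse-event case there is only an example. Sections 8.4, 9.1.4 and 9.2.3 all point to continued observation, the early-termination visit covers the assessments of a scheduled visit, and Visit 3 records infection. The day-42 and 1-year follow-up apply to both arms.

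Most of this stands. A reader might infer that follow-up will be lost selectively in the decolonization arm, that only that arm has procedures to follow, or that an ITT analysis becomes impossible. The document supports none of these. Loss is a risk that the text permits, not a stated consequence; the asymmetry lies in adherence demands, not in all procedures; and ITT can be compromised but is not ruled out. Nor does the text support assuming that 10 to 30% of the arm is removed. That does not fit a rule for rare use, and 9.2.3 expects no major drop-out.

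What the reply does not remove: the exclusion ground is written down, the person applying it knows the arm, and the option of stopping treatment while staying in the study is only permissive. Nothing says that a patient who declines or does not complete decolonization remains in follow-up.

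**Conclusion.** The point holds as a permitted risk and an internal inconsistency. Section 7.4 allows post-randomization exclusion on a ground that bears almost wholly on one arm of an unblinded trial. It also leaves open whether refusing the intervention means leaving follow-up, with deletion of data under 6.1.2. This conflicts with 11.3.2 and with the requests for continued data collection in 7.4, 8.4 and 9.2.3.

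The size and direction of bias cannot be derived from the document. Under the stated assumptions (no true effect, removed patients at twice the adherers' risk), removal of 2 to 5% gives 0.2 to 0.5 points of false benefit against a 5-point target, and a one-sided false-positive rate of 3.2 to 4.4%. At 10% removed the figures are 0.9 points and 6.8%. With equal risk there is no bias. This should be fixed; the permissive wording and small plausible scale do not make it a critical defect.

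**What to change.** - In 7.4, delete failure to follow study procedures as a ground for exclusion from the study.
- In 7.4, state that declining or not completing decolonization is recorded as non-adherence and is not withdrawal of consent. Such patients stay in follow-up for the 6-week and, with an implant, the 1-year primary outcome, unless they explicitly withdraw consent to data collection.
- In 9.1.4, name SSI and wound revision among the items recorded.
- Reconcile 6.1.2, 7.4, 8.4, 9.1.4, 11.3.2 and 11.4, so that deletion of data follows only explicit withdrawal of consent to data collection and non-adherent patients remain in the ITT set.

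The cost is a change of protocol wording and its approval. No visits are added, because 9.2.3 describes all study visits as part of routine surgical care. The change is best made before enrolment, since outcomes not collected or already deleted cannot be recovered at analysis.
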